#### Proposed statistical analyses

Data normality will be evaluated with the Kolmogorov-Smirnov test. The comparison of the clinical control and other variables will be made by a two-way analysis of variance (ANOVA) with repeated measures followed by the Student-Newman Keuls post-hoc test to identify significant differences. The level of statistical significance will be set at 5% (p < 0.05).

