[12] and corticosteroid consumption
[13], exacerbation episodes and asthma symptoms
[13]. Moreover, breathing exercises have been shown to improve HRQoL
[14] and expiratory peak flow values
[15]. Breathing exercises also reduce the levels of anxiety and depression
[16], asthma symptoms
[17], the use of relief medication
[14], exacerbation episodes and airway hyperresponsiveness
[18].

The research questions were:Which exercise intervention is more effective to improve clinical control in patients with moderate and severe asthma?Which are the mechanisms involved to improve clinical control in both interventions?

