## Method

### Design

This trial was designed as a prospective, comparative, blinded, and randomized clinical trial with 2 groups that will receive distinct interventions. See the study design in Figure 
1.

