**Figure 1 Fig1:**
[figure not shown]
**Study flow chart: after inclusion, patients will be evaluated twice.** In visit one clinical control, pulmonary and systemic inflammation and psychosocial variables will be measured and in visit two pulmonary function, maximal exercise capacity, thoracoabdominal kinematics and autonomic control will be assessed; afterwards subjects will begin the educational program, consisting of two classes: one related to the disease and skills concerning medication and self-monitoring, and other related to control of external factors and peak flow meter usage. Only then, subjects will be randomized into aerobic or breathing group for 24 sessions, after which they will be revaluated.

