### Outcome measures

#### Primary outcome

The asthma control questionnaire (ACQ)
[22] will be used to assess asthma control. We will compare the differences between the 2 interventions in the absolute change in asthma control post-intervention. This questionnaire is validated to measure asthma control in adult patients and have been validated to Brazilian Portuguese
[23]. ACQ is a simple instrument and is easy to use that quantifies the following asthma symptoms: nocturnal and morning symptoms, limitation of daily activities, dyspnea and wheezing, and the use of medication (short-acting β_2_-agonist). Patient’s will be scored on a scale ranging from 0 to 6 (0 = without limitation and 6 = maximum limitation). The clinical score of forced expiratory volume (% of predicted, pre-bronchodilator) will be scored on similar scale. The items will be calculated, and the scores of the ACQ will be the average from 7 items between 0 (fully controlled) and 6 (severely uncontrolled). The cutoff will be adopted from previously developed studies, considering controlled (ACQ <0.75 points), not well controlled or poorly controlled asthma (ACQ > 1.5 points). A clinically effective treatment results in a 0.5 point decrease in the score after the intervention
[24].

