#### Analyses population and missing data

All main analyses will use intention-to-treat, considering all patients as randomized regardless of their adherence to the treatment protocol or completion of post-intervention assessments. These analyses will be used to define the efficacy of aerobic and breathing exercises to influence asthma control.

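### The plan identifies differences by Student-Newman-Keuls comparisons, none of which is the primary contrast, and does not name the arm-by-time test that answers the primary question

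*Protocol article*

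**What the plan says.** The research question in the Background is comparative: "Which exercise intervention is more effective to improve clinical control in patients with moderate and severe asthma". The Primary outcome section turns it into an estimand: "We will compare the differences between the 2 interventions in the absolute change in asthma control post-intervention".

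Under Proposed statistical analyses, clinical control and the other variables are to be compared by a "two-way analysis of variance (ANOVA) with repeated measures", "followed by the Student-Newman Keuls post-hoc test to identify significant differences". The section does not say which ANOVA term carries the primary conclusion, nor whether the post-hoc step depends on any term being significant.

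Three other places bear on how results would be read:

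- Analyses population and missing data, on the intention-to-treat analyses: "These analyses will be used to define the efficacy of aerobic and breathing exercises to influence asthma control".
- Primary outcome, on the instrument's threshold: "A clinically effective treatment results in a 0.5 point decrease in the score after the intervention". This is a pre-post criterion.
- Design and the Figure 1 legend: the trial is a "randomized clinical trial with 2 groups that will receive distinct interventions", both of them active. After the two baseline visits, "afterwards subjects will begin the educational program, consisting of two classes". Randomisation follows the classes, and reassessment follows the 24 sessions.

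**The concern.** The question is whether one exercise changes ACQ more than the other. A procedure that compares cell means in pairs answers other questions: did this arm change, did that arm change, do the arms differ at one visit. If one arm's fall is significant and the other's is not, that is no evidence that the falls differ.

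Nor does a significant fall within an arm show efficacy. There is no untreated or education-only arm, and baseline ACQ precedes the education classes. Each arm's fall therefore mixes the exercise with education, regression to the mean and time. The sentence about defining efficacy makes that reading easier. At stake is a report that favours one exercise, or calls each effective, when the randomised comparison shows neither.

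**Working it through.** The plan gives no figure of its own on this point to reproduce. The check has an algebraic part and a simulation.

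**1. Which contrast answers the question.** Write A0, A1 for the aerobic means before and after, and B0, B1 for the breathing means. The primary contrast is

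D = (A1 − A0) − (B1 − B0).

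With two time points, the interaction F in the planned ANOVA equals the square of the two-sample t on change scores, so the ANOVA contains the test of D = 0.

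**2. What Student-Newman-Keuls can add.** Each factor has two levels, so neither main effect needs a post-hoc test. Only the four cell means remain, with six pairs: A0–A1, B0–B1, A0–B0, A1–B1, A0–B1, A1–B0. D involves all four means, so none of the six equals D. That the step is meant for the four means is an inference, but it is the only non-redundant use of it in this design.

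**3. Inputs for the simulation.**

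- 20 per arm: the 40 evaluable patients in the Sample size section, halved. The allocation ratio is not stated, so 1:1 is assumed.
- SD 0.72: from the Sample size section, taken as the SD of change. The section does not say whether it is that or the SD of the score.
- Pre-post correlation 0.5, varied from 0.3 to 0.7: assumption.
- Within-patient error term for the pairwise comparisons: assumption.
- The same true improvement in both arms (0.25, 0.33 or 0.50 points), so D = 0: scenario.

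**4. Standard errors at 20 per arm.**

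- One arm's change: 0.72/√20 = 0.161.
- D: 0.72 × √(2/20) = 0.228.
- Within-patient mean square: 0.72²/2 = 0.259. It gives every pair a standard error of √(2 × 0.259/20) = 0.161.
- Post-intervention pair A1–B1, correct value: at correlation 0.5 the SD of a single score is 0.72/√(2 × 0.5) = 0.72, so the standard error is 0.72 × √(2/20) = 0.228. The within-patient term understates it by a factor of 0.228/0.161 = 1.41, which is why that pair is declared significant too often.

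**5. Results at correlation 0.5, no true difference between arms.**

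| Event | No gate | Only after a significant interaction |
|---|---|---|
| Exactly one arm significant, improvement 0.25 / 0.33 / 0.50 | about 29% / 39% / 31% | about 4% |
| Post-intervention between-arm pair significant | about 11% to 15% | about 2% |
| Interaction test rejects | about 5% | – |

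Gating on the time effect instead hardly helps: exactly one arm is significant in 27%, 38% and 31%.

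**6. Sensitivity.** Over correlations 0.3 to 0.7 and improvements 0.25 to 0.50, without a gate, exactly one arm is significant in 26% to 43% of trials at 20 per arm and in 22% to 45% at 24 per arm. At correlation 0.7 the false post-intervention pair rises to about 21% to 27% without a gate, and is 1.8% to 2.6% with the interaction gate.

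**7. Within-arm efficacy.** If both arms fall by 0.50 for a shared reason such as education or time, at least one arm shows a significant improvement in 91% to 93% of trials at 20 per arm, even if neither exercise does anything.

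**The case against.** The strongest reply is that the ANOVA comes first and already holds the right test, and that a post-hoc test is naturally read only after a significant interaction. On that reading the false findings stay at or below 5%. This stands as far as it goes: the ungated rates belong to one reading of an ambiguous sentence. The article does not state the gate, however, and a gate on the time effect, equally compatible with the text, leaves the rates almost unchanged.

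A second reply is that a condensed article may leave the primary model term to the statistical analysis plan. Silence on the term alone would indeed be no finding. But the article does fix a step for finding differences, and that step does not contain the primary contrast.

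A third reply is that the efficacy sentence is loose wording in a paragraph on the analysis population, and that the 0.5-point sentence explains the instrument and is not a test rule. That is fair. Neither sentence commits the investigators to a within-arm claim; they only make one easier to draw.

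A reader might also infer more than the documents support:

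- *That the planned ANOVA cannot answer the question.* It can, through its interaction term.
- *That the protocol has a rule under which significance in one arm alone means superiority.* No section says so.
- *That taking baseline before education biases the comparison of the arms.* Education precedes randomisation and is common to both arms, so it does not bias the difference in change. It undermines only within-arm claims.
- *That the sample size shows an intention to test within arms.* The Sample size section states no such intention, and its adequacy is a separate matter.

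**Conclusion.** The point holds in this form. The protocol defines a between-arm difference in ACQ change, plans a model that contains its test, but does not give that test the decision and relies on pairwise comparisons that cannot express it. That part is algebra and needs no assumption beyond the two-arm, two-visit design.

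The size is conditional. It needs the post-hoc step to be read without an interaction gate, and the discordance rate becomes an error rate only if someone takes one-arm-only significance as a difference between arms. The rate for the post-intervention pair depends further on the within-patient error term and on the correlation. With an interaction gate, little excess error remains, but the post-hoc step still adds nothing to the primary answer.

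Within-arm efficacy cannot be established by this design under any reading of the analysis section.

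**What to change.** 1. In Proposed statistical analyses, name the between-arm difference in ACQ change as the sole primary test, with its 95% CI, at two-sided 5%. Use the arm-by-time contrast or, preferably, post-intervention ACQ compared between arms with adjustment for baseline ACQ.
2. Delete the Student-Newman-Keuls step.
3. Report the change within each arm descriptively, without p-values.
4. In Analyses population and missing data, replace the stated purpose of defining efficacy with: *to estimate the comparative effectiveness of aerobic versus breathing exercise*.

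The Study status section says that the study is ongoing and data are being analysed, so the change should be dated, with a note of whether ACQ results by arm had been seen.

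The cost is wording. No visit, measurement or patient is added. The sponsor gives up within-arm efficacy claims, which the design could not support.

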#### Analyses population and missing data

All main analyses will use intention-to-treat, considering all patients as randomized regardless of their adherence to the treatment protocol or completion of post-intervention assessments. These analyses will be used to define the efficacy of aerobic and breathing exercises to influence asthma control.

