**Methods/design:**

This is a prospective, comparative, blinded, and randomized clinical trial with 2 groups that will receive distinct interventions. Forty-eight asthmatic adults with optimized medical treatment will be randomly divided into either aerobic (AG) or breathing exercises (BG). Patients will perform breathing or aerobic exercise twice a week for 3 months, totalizing 24 sessions of 40 minutes each. Before intervention, both groups will complete an educational program consisting of 2 educational classes. Before and after interventions, the following parameters will be quantified: clinical control (main outcome), health related quality of life, levels of anxiety and depression, daily living physical activity and maximal exercise capacity (secondary outcome). Hyperventilation syndrome symptoms, autonomic nervous imbalance, thoracoabdominal kinematics, inflammatory cells in the sputum, fraction of exhaled nitric oxide (FE_NO_) and systemic inflammatory cytokines will also be evaluated as possible mechanisms to explain the benefits of both interventions.

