### Data analysis

#### Sample size

It was estimated based on a minimal important difference of 0.5 points on the ACQ questionnaire with a standard deviation of 0.72
[38]. A sample size of 40 patients was required for a 5% level of significance with 80% power using a two-tailed *t* test. An estimated drop-out rate of 20% was used to determine the final target sample size of 48 patients.

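### As written, the repeated-measures ANOVA cannot include the randomised patients without a post-intervention assessment whom the intention-to-treat statement promises to count

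*Protocol article*

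**What the plan says.** All references are to the protocol article.

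- **Population** (*Analyses population and missing data*): every main analysis is to be by intention-to-treat, and the article describes the set it has in mind as "considering all patients as randomized regardless of their adherence to the treatment protocol or completion of post-intervention assessments". The heading covers missing data, but the text gives no rule for a missing value.
- **Method** (*Proposed statistical analyses*): clinical control and the other variables are compared by a "two-way analysis of variance (ANOVA) with repeated measures followed by the Student-Newman Keuls post-hoc test". No other model is named.
- **Primary contrast** (*Primary outcome*): "We will compare the differences between the 2 interventions in the absolute change in asthma control post-intervention".
- **Measurement times** (abstract, *Methods/design*): "Before and after interventions, the following parameters will be quantified: clinical control (main outcome" and others. The Figure 1 legend agrees: "subjects will be randomized into aerobic or breathing group for 24 sessions, after which they will be revaluated". That gives one value before and one after.
- **Expected loss** (*Sample size*): "An estimated drop-out rate of 20% was used to determine the final target sample size of 48 patients".

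**The concern.** The population statement expressly keeps patients who have no post-intervention assessment. The method statement names an analysis that, on two time points, has no place for them. Both are explicit, so this is a conflict between two stated elements and not simply a detail left out.

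What is at stake is the meaning of the primary result. If the ANOVA is run on the data as collected, the ACQ comparison describes patients who returned for reassessment but is reported as covering everyone randomised. If patients are lost at different rates in the two arms, or if those lost do differently in the two arms, the two comparisons can differ.

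**Working it through.** **Why the ANOVA needs both values.** With two groups and two time points, the group-by-time F statistic is the square of the t statistic comparing individual changes (post minus pre) between groups. A patient without the post value has no change and cannot enter. As a check, a standard repeated-measures ANOVA routine was given simulated data for 48 patients, some without a post value. It stopped with an error that the data were unbalanced.

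**The plan's own figures.**
- The step from 40 to 48 is reproduced by 40 × 1.20 = 48. (Dividing by the retained fraction gives 40 / 0.80 = 50.) Either way, the allowance treats drop-outs as adding nothing to the analysis, which fits a both-values analysis better than the intention-to-treat statement.
- The 40 itself is not reproduced for the between-group contrast. A difference of 0.5, SD 0.72, two-sided 5% and 80% power need 33 per arm (normal formula) or 34 (exact t), so 66 to 68 in total. That is a separate matter, and this point does not depend on it.

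**Patients lost from the primary contrast.** 48 × 0.20 = 9.6, about 10. 48 − 10 = 38 remain, or 19 per arm if allocation is 1:1 (assumed; the ratio is not stated).

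**Precision.** Exact two-sample t test, difference 0.5, with 0.72 taken as the SD of the change (assumed; the article does not say):

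| Patients analysed | Power |
|---|---|
| 48 (24 per arm) | 65% |
| 40 (20 per arm) | 57% |
| 38 (19 per arm) | 55% |

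The 65% applies only if all 48 outcomes are actually observed. No model restores it by itself.

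**Bias, on assumed inputs.** Suppose drop-outs in each arm do g ACQ points worse than completers in the same arm, with d0 and d1 drop-outs among 24 per arm. The completers' difference then departs from the all-randomised difference by g × (d1 − d0) / 24.

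| Drop-outs by arm | g = 0.25 | g = 0.50 | g = 0.75 |
|---|---|---|---|
| 5 v 5 | 0 | 0 | 0 |
| 3 v 7 | 0.04 | 0.08 | 0.13 |
| 0 v 10 | 0.10 | 0.21 | 0.31 |

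**One worked case (assumed).** Drop-out is 30% in one arm and 10% in the other. Completers improve by 0.5 in both arms and drop-outs by 0.
- Completers: −0.5 − (−0.5) = 0.00.
- All randomised: 0.70 × (−0.5) − 0.90 × (−0.5) = −0.35 + 0.45 = 0.10, which is 0.10 / 0.5 = 20% of the plan's minimal important difference.

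**What different ways of handling the gap would report in that case.** If drop-out is unrelated to baseline, imputing within arm gives drop-outs the completers' change, so each arm averages −0.5 and the difference is again 0.00. Carrying baseline forward gives 0.10. Carrying forward has its own cost: with equal 20% drop-out and a completers' difference of 0.5, it reports 0.5 × (1 − 0.20) = 0.40. The choice of technique therefore moves the primary estimate.

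**The case against.** The strongest reply is that the contradiction is inferred. No sentence says that incomplete cases are deleted. A commitment to keep patients without a post value may imply that values will be filled or modelled, and a repeated-measures ANOVA on filled data would include all 48. A condensed article may leave that technique to a fuller document. This stands as a limit: the point holds only as written, with no imputation or mixed model named. It does not dissolve the point, because the article fixes both the population and the method, and the two do not fit together.

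Three stronger readings are tempting, and the documents support none of them.

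- **That the arm comparison will be biased.** A reader might infer this from how different treadmill training and breathing exercise are. The article gives no drop-out rate or reason by arm, both arms have the same session schedule, and the *Discussion* cites evidence that physical training is well tolerated. It also mentions negative attitudes toward exercise, so unequal drop-out is possible but not shown.
- **That patients who stop attending have no defined reassessment, or that slow attenders are measured late.** The Figure 1 legend does tie reassessment to the sessions. However, the abstract sets twice-weekly sessions for 3 months and *Breathing exercise* sets three one-month phases, so a nominal 3-month point exists. Nothing says that make-up sessions extend follow-up.
- **That a mixed model or imputation would cure the illustrated bias.** Both assume data missing at random, and the worked case shows that the 0.10 stays hidden.

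**Conclusion.** The conflict is real in conditional form. As written, the intention-to-treat set in *Analyses population and missing data* cannot be produced by the ANOVA in *Proposed statistical analyses*. About 10 of 48 patients would drop out of the primary ACQ contrast at the plan's own rate, and the result would carry a label that it does not meet. This rests on one pre and one post value per patient, which the article states, and on no missing-data technique being used, which is how the text reads.

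The size of any bias is not established. It is zero with equal drop-out and equal shortfall, 0.10 points in the worked case, and up to 0.31 at the extreme of the assumed range. A reader might infer that the trial has deliberately planned a completers analysis. The text does not say so; it leaves two statements that have to be reconciled.

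**What to change.** 1. In *Proposed statistical analyses*, make the primary ACQ analysis one of these:
   - a likelihood-based mixed model on all randomised patients, with arm, time and arm-by-time terms and baseline means constrained equal; or
   - ANCOVA adjusted for baseline ACQ, with multiple imputation by arm.
2. State the missing-at-random assumption. Add a delta-adjusted sensitivity analysis in which drop-outs show no improvement, since the primary model does not address that case.
3. If neither model is adopted, call the analysis complete-case and do not label it intention-to-treat.
4. Where feasible, seek the post-intervention ACQ at the nominal 3-month point from patients who stop training.

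**Cost.** Items 1 to 3 need new wording, one standard model and one extra analysis, and they make the result rely on a stated missing-data assumption. Item 4 is more than a short questionnaire: the 7-item score in *Primary outcome* includes pre-bronchodilator FEV1, so the full score needs spirometry. *Study status* says the trial is ongoing and data are being analysed, so item 4 may be too late for some patients, and any change of analysis should be dated and documented.

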## Discussion

Asthma symptoms have a significant impact on patient’s life and the proper clinical treatment is very important to reduce those symptoms; however, sometimes clinical control is difficult, despite the appropriate amount of prescribed medication. Aerobic and breathing exercises have been considered important as complementary therapies in addition to the pharmacological treatment mainly for patients with controlled or partially controlled asthma, because they improve disease control
[1]. In addition, asthmatic patients have 2 main clinical conditions that support the importance of these non-pharmacological interventions: they are more prone to be physically deconditioned compared with their peers and they also have a high prevalence of hyperventilation symptoms
[39]. Because of that, asthmatic patients tend to face more negative attitudes toward exercise and present higher levels of anxiety and depression
[40, 41].

The proposal of our study, comparing the benefits of aerobic and breathing exercises training on clinical control, seems quite relevant because even if both techniques have similar effects in reducing asthma symptoms, we will further investigate some mechanisms in order to understand how patients develop their benefits at each and every intervention. There is evidence that aerobic exercises improve cardiovascular fitness, resistance to stress and health related quality of life (HRQoL) as well as decrease dyspnea, incidence of exercise-induced bronchospasm, use of corticosteroids, inflammatory parameters, anxiety and depression related to asthma
[9]. A recent Cochrane review confirmed these benefits and also demonstrated that physical training can be well tolerated among people with asthma
[42]. These studies show us that there was some evidence to suggest that physical training may have positive effects on HRQoL. Therefore, exercise training can also improve daily living physical activity and reduce dyspnea
[43]. In our opinion, the improvement in aerobic capacity will reduce airway inflammation levels improving clinical control.

In addition, the practice of breathing exercises have been shown to improve HRQoL, peak expiratory flow, asthma symptoms as well as to reduce the levels of hyperventilation symptoms, anxiety and depression and medication consumption
[44]. A recent Cochrane review demonstrated that individual trials reported positive effects of breathing exercises, but authors concluded that no reliable conclusions could be drawn concerning the use of breathing exercises in asthma control
[10]. In our opinion, breathing exercise will reduce anxiety and depression levels, which seem to be associated with dysfunctional breathing such as hyperventilation
[16] normalizing, thus, the autonomic system
[45].

Although the benefits of breathing and aerobic exercises have been extensively investigated, the comparison between both interventions has never been performed. Then, this study will be the first to make this comparison and to investigate several physiological mechanisms which may be triggered either by aerobic training or by breathing exercises. Furthermore, the findings of our results will allow us to understand its application and suitability to patients that will have more benefits for every intervention optimizing its effect.

